# STUDY POPULATION

## Eligibility criteria

Inclusion:

We will train a total of 24 physicians. The intervention will be assessed by interviewing a total of 400 patients who present to the emergency department of the University Hospital Basel with chest pain or abdominal pain and who are seen by one of the study participants.

We will use the following exclusion criteria concerning patients with chest pain (see Figure 3):

- Patients *younger than 18 years of age* will not be recruited because of limited ability to provide informed consent.
- Patients with *limited ability to communicate in German* (the default language at the hospital) will not be recruited to exclude additional confounds related to language proficiency.
- Patients with *dementia* will not be recruited to avoid additional confounds arising from pathological memory deficits.
- Patients with *increased troponin level*, an indicator of myocardial infarction, will not be recruited to minimize stress on these more vulnerable patients.
- Patients with none of five *cardiovascular risk factors* (cvRF; smoking history, diabetes, hypertension, dyslipidemia, age above 50 years, or family history of coronary heart disease) will not be recruited because chest pain symptoms in such patients are typically indicative of diagnoses unrelated to coronary heart disease, requiring a very different follow-up and health management recommendations (e.g., in the case of an anxiety disorder).

*
[figure not shown]
*

Figure 3. Decision Tree for Participant Exclusion/Inclusion in the Intervention Assessment

We will use the following exclusion criteria concerning patients with abdominal pain:

- Patients *younger than 18 years of age* will not be recruited because of limited ability to provide informed consent.
- Patients with *limited ability to communicate in German* (the default language at the hospital) will not be recruited to exclude additional confounds related to language proficiency.
- Patients with *dementia* will not be recruited to avoid additional confounds arising from pathological memory deficits.

## Recruitment and screening

All physicians participating in the study will be asked to contact a member of the study team about any pending discharge communication with a patient suffering from chest pain or a patient suffering from abdominal pain. Eligible participants (see 7.1) will be asked to give written consent to participate in the study. There will be no monetary compensation for the participation.

## Assignment to study groups

The first communication skills training will be randomly assigned by *randomizer.org*. After knowing which communication skills training will be the first, the trainings will be alternately assigned.

## Criteria for withdrawal / discontinuation of participants

If participants withdraw their informed consent, are non-compliant or suffer from unexpected health problems they will be withdrawn from the study. If the investigator or a physician have concerns about safety issues the participant will be withdrawn from the study as well.

# STUDY INTERVENTION

## Identity of Investigational Products (treatment / medical device)

We aim to examine the advantages of an information-structuring skills training for physicians (compared to an emotion skills training) on discharge communication and associated patient outcomes.

### Experimental Intervention (treatment / medical device)

Communication skills training: information structuring skills training

### Control Intervention (standard/routine/comparator treatment / medical device)

Communication skills training: emotional skills training

### Packaging, Labelling and Supply (re-supply)

NA

### Storage Conditions

NA

## Administration of experimental and control interventions

### Experimental Intervention

Communication skills training: information structuring skills training

### Control Intervention

Communication skills training: emotional skills training

## Dose / Device modifications

NA

## Compliance with study intervention

NA

## Data Collection and Follow-up for withdrawn participants

Patients will be excluded if informed consent is withdrawn or the patient doesn’t participate in follow-ups.

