| **Number of Participants with Rationale (if no Power Analysis conducted):** | Within three months 50 patients with chest pain and 50 patients with abdominal pain will be recruited. Including 4 groups with 100 patients each this sums up in 400 patients in one year. Sample of 400 gives acceptable power of .8 for comparison of two groups.  We based our sample sizes on calculations based on previous studies that compared an information structuring intervention relative to treatment as usual and suggest a medium effect size d = .59 for the intervention. To compute power for our planned analysis we conducted simulations in which we generated data using the means and standard deviations as those observed in the previous study but let patients be sampled from an homogenous pool of 6 physicians and varied the sample sizes per intervention group from 40 to 120. We then conducted 1000 repeated iterations for each sample size and analysed the data with a mixed effects model of patient’s recall clustered by physician and calculated the frequency of observing a significant effect of intervention for each sample size. A sample size of 100 participants per condition guarantees an appropriate power of over .9. Please note that while a smaller sample sizes per condition of over 50 would guarantee satisfactory power levels above .8, having a larger initial sample size is of importance given the possible attrition rates between the first measurement point (immediately after discharge) and the two planned follow-ups (over the telephone). Specifically, our desired sample size guarantees that we would have power above .9 for the analysis of the follow-up measurements in the face of 25% attrition rates over measurement occasions. |
| **Study Duration:** | The study will start at 02/01/2015 and will end at 31/12/2015 (=1 year). |
| **Study Schedule:** | First contact with study participants will be the 02/01/2015 when [name]. [name] will teach the first cohort of physicians. The last contact with participants will be the last doctor patient communication (approx. 31/12/2015). |
| **Investigator(s):** | [name]. [name]  Universitätsspital Basel  Interdisziplinäre Notfallstation  [name]  4031 Basel  Schweiz  PD [name]  Universitätsspital Basel  [name]  4031 Basel  Schweiz  [name]  Interdisziplinäre Notfallstation  [name]  4031 Basel  Schweiz |

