# STUDY OUTCOMES

## Primary Outcome

Participants’ recall of discharge information will be assessed after the discharge communication and 1 week later. We measure this primary outcome to check whether the intervention was successful or not. We measure the recall 1 week and 30 days later to check the long-term effect of the intervention.

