# STUDY ASSESSMENTS

## Study flow chart(s) / table of study procedures and assessments

Eligible participants (see section on Participants above) will be asked to give written consent to participate in the study and complete a pre-discharge assessment. The pre-discharge assessment will take about 15 minutes and aims to collect basic demographic measures concerning each patient as well as a number of other measures that will serve as covariates in the analysis, such as patients’ health status, memory ability, state anxiety, state depression, and medical knowledge.

Immediately after the discharge communication event, patients will be interviewed for up to five minutes to assess recall of information provided during the discharge consultation and to assess patients’ satisfaction with the encounter.

Finally, two brief interviews of 5–10 minutes will be conducted over the phone seven days after discharge and 30 days after discharge to retest recall of discharge information, thus assessing the reliability of the main outcome measure and the time component of recall.

For more information see also section “study schedule”.

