|  | State anxiety and depression | German version of the Hospital Anxiety and Depression Scale (HADS-D),^31^ a brief instrument containing two scales of 7 items assessing state anxiety and depression. |
|  | Medical knowledge | Multiple-choice test consisting of 6 questions of increasing difficulty developed by our research team. |
| Interview | Immediate recall | Patients will be asked to freely recall all information provided immediately after the discharge event, “Can you tell me all the information your physician just provided?”, and repeated use of prompts, “Was there any other information you can recall?” until the patient cannot recall any more information. |
|  | Satisfaction | Once patients cannot recall any additional information, they will be asked to characterize their satisfaction with the discharge communication event and physician. Specifically, we will previously developed items (see Study 4) asking patients to rate on a scale from 1 to 10 the (1) physician’s comprehensibleness, (2) information structuring, and (3) willingness to recommend the physician to family and friends. |
| Telephone Interview | Delayed recall | Patients will be asked to freely recall all information mentioned in the discharge event, “Can you tell me all the information your physician provided when you left the emergency department?”, and repeated use of prompts, “Was there any other information you can recall?” until the patient cannot recall any more information. In addition, patients will be asked whether they have received additional information from their general practitioner since discharge. |
|  | Adherence to recommendations | Patients will be asked to list all the physician recommendations that they have actively pursed, “Can you tell me which of your physician’s recommendations you have pursued?”. |
|  | Overall assessment | German version of the Patient Reactions Assessment (PRA-D),^32^ composed of three 5-item scales designed to measure information, affective, and communication components of physician–patient communication. |

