### Assessments in participants who prematurely stop the study

Data from the participants won’t be used for the study. There won’t be any disadvantages for the participant.

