## Planned Analyses

The evaluation of the effects of the two training programs will be conducted using mixed-effects model.^33^ Mixed-effects models are statistical models containing both fixed (e.g., intervention program) and random (e.g., patient) effects and are used in a variety of disciplines including medical and social sciences, where repeated measurements are made on the same statistical units or on clusters of related statistical units. Specifically, our analysis will take into account the fact that physicians belong to particular clusters (see Study Design) and the same physician treats several patients, by clustering physicians by training program and patients by physician. These multivariate analysis methods also allow for simultaneous statistical adjustment for covariates of interest, including patient characteristics, such as age, memory ability, and so on. Similar models will be used to estimate the effect of the training programs on patient satisfaction, and adherence to discharge recommendations.

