### Datasets to be analysed, analysis populations

The analysis population will be patients with chest pain and patients with abdominal pain. Evaluation groups will be patients having a discharge communication with a physician trained in structured information skills or physicians trained in emotion skills.

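### Section 8.5 excludes patients who do not take part in follow-up, which as written discards immediate recall already measured and conflicts with the synopsis and section 11.4.1

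*Protocol*

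**What the plan says.** Section 8.5 of the protocol consists of one sentence: "Patients will be excluded if informed consent is withdrawn or the patient doesn’t participate in follow-ups". Section 9.2.5, on participants who stop prematurely, says: "Data from the participants won’t be used for the study". Section 11.5, on missing data and drop-outs, lists grounds for withdrawal and has no rule that keeps interviews already given.

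On timing, section 5.1 says of the primary outcome: "Participants’ recall of discharge information will be assessed after the discharge communication and 1 week later". It then describes the one-week and 30-day measurements as a check of the long-term effect. Table 5 puts immediate recall in the interview on the day: "Patients will be asked to freely recall all information provided immediately after the discharge event". The calls come later; section 9.1 says "two brief interviews of 5–10 minutes will be conducted over the phone seven days after discharge and 30 days after discharge".

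Two other places describe the analysed patients differently. The sample size rationale in the synopsis speaks of "possible attrition rates between the first measurement point (immediately after discharge) and the two planned follow-ups" and claims power after 25% attrition for the follow-up measurements only. Section 11.4.1 says "The analysis population will be patients with chest pain and patients with abdominal pain", with no condition that follow-up be completed.

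**The concern.** The conjunction in section 8.5 makes non-participation in follow-up a ground for exclusion in its own right, next to withdrawal of consent. What is excluded is the patient, not the missed call. A patient who consented, had the recorded discharge talk and gave a full immediate recall interview would then leave the study because of something that happened one to four weeks later.

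That event comes after the physician was trained and after the outcome was measured. It may be related to memory, to engagement, or to how the talk went. If it is, and not equally in both arms, the immediate-recall comparison is made between two selected groups, although nothing is missing for that comparison. Section 7.4 does not cover this case explicitly: it lists withdrawn consent, non-compliance, health problems and safety concerns. Missed follow-up is named only in section 8.5.

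**Working it through.** **1. Does the rule reach observed primary data?** Immediate recall is part of the primary outcome (section 5.1). It is collected on the day of discharge (Table 5), and follow-up starts at day 7 (section 9.1). So a patient can have a complete immediate value and still meet the exclusion ground in 8.5. Read with 9.2.5, that value is dropped.

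**2. Is this consistent with the rest of the protocol?**

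| Place | Who counts for immediate recall |
| --- | --- |
| 8.5 with 9.2.5 | only patients who take part in follow-up |
| Synopsis, sample size | everyone; attrition arises after this point |
| 11.4.1 | all chest pain and abdominal pain patients |

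These cannot all hold.

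**3. The plan's power figures first.** Inputs from the synopsis: d = .59; 100 per condition gives power over .9; more than 50 gives above .8; above .9 for the follow-ups after 25% attrition. Two-sided alpha of .05 is my assumption, because none is stated. Ignoring clustering, power = Φ(d√(n/2) − 1.96).

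- n = 100: .59 × 7.071 − 1.96 = 2.21, power .987
- n = 75 (25% lost): .59 × 6.124 − 1.96 = 1.65, power .951
- n = 50: .59 × 5 − 1.96 = .99, power .839

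The stated figures are reproduced on this basis. The power statement is not in error.

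**4. Patients lost from the immediate comparison.** Planned: 400, that is 200 per training.

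- 25% lost in total: 400 × .75 = 300 (150 per arm)
- 25% lost at each call, both calls required: 400 × .75 × .75 = 225 (about 112 per arm), a 44% loss

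The second case is an assumption. Section 8.5 does not say whether one missed call is enough, and the synopsis does not say whether 25% applies per call.

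**5. Power after that loss** (two arms, clustering ignored, so not the trial's actual power):

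| Per arm | d = .59 | d = .4 |
| --- | --- | --- |
| 200 | >.999 | .979 |
| 150 | .999 | .932 |
| 112 | .993 | .846 |

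The d = .4 column uses the effect size in section 11.2, where it is attached to a comparison of four groups; those values come from the noncentral t. Only at the 100 per condition of the synopsis simulation does the worst case fall below .9: n = 56 gives .59 × 5.292 − 1.96 = 1.16, power .877.

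**6. Selection bias, illustration only.** No selection strength is given in the protocol, so every input here is assumed. Let recall correlate ρ with a latent tendency to stay, and let r be the retention in an arm. Completers' mean recall is then shifted upward by ρ·φ(Φ⁻¹(r))/r, in SD units.

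- Equal retention and equal ρ: the shifts cancel and .59 stays .59.
- ρ = .2, retention 80% (structuring) against 70%: shifts .070 and .099, so .59 + .070 − .099 = .56.
- ρ = .5, retention 85% against 65%: shifts .137 and .285, so .59 + .137 − .285 = .44. With the retention reversed, .59 + .285 − .137 = .74.

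A second assumed model uses logistic completion on recall at 75% overall. If the odds of completing double per SD of recall in both arms, a true .40 becomes .37; if they triple, .34. Under a true null, dependence in one arm only (odds ratio 1.5 per SD) gives about .10 SD in either direction.

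**The case against.** Section 8.5 stands under a heading about withdrawn participants. It does not say whether exclusion means removal from the analysis or only from further participation, nor whether one or both calls must be missed. Section 9.2.5 is about stopping prematurely, and no passage says that missing a call counts as that. Section 11.4.1, which is the analysis-set section, has no completer restriction. This stands in part: a reader might infer that a completers-only primary analysis has been settled, and the document does not support so firm a reading. What it does support is that 8.5 and 9.2.5, taken as written, remove the data, that no passage keeps them, and that two other passages disagree.

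Section 5.1 also names the one-week measurement under the primary outcome, so a patient who misses that call may lack part of the primary data. That is correct. The point therefore concerns the immediate-recall comparison, not every form of the primary analysis.

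A reader might also infer that the exclusion defeats the purpose of the planned mixed model. Section 11.4 justifies the model by clustering and covariate adjustment. It describes such models only generally as used "where repeated measurements are made on the same statistical units or on clusters of related statistical units" and makes no claim about incomplete follow-up. The narrower statement holds: such a model can use patients with some interviews missing, so the exclusion is not needed for it.

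Finally, section 6.3 says patients are blind to condition, which makes strongly arm-specific dropout less likely. It does not rule it out, because the training is meant to change the talk that patients experience.

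**Conclusion.** The concern holds as a conflict within the protocol and as an avoidable source of bias. As written, 8.5 with 9.2.5 removes observed immediate recall and makes that comparison conditional on later participation, against the synopsis and 11.4.1.

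The sample for immediate recall falls from 400 to about 300 at 25% loss, or to 225 under the stricter assumption. Two stronger conclusions are tempting and not supported. One is that the trial becomes underpowered: at the planned 200 per training, the calculated power stays at about .99 or higher for d = .59 and above .8 for d = .4, with clustering ignored. The other is that a bias of known size or sign follows: the illustrations range from none to about .15 SD in either direction, and rest entirely on assumed selection. The defect is that the validity of the comparison is made to depend on equal selection in the two arms, with no gain in return. Because the protocol states a rule here, this is not a detail left to a later analysis plan; a plan that kept these patients would contradict it.

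**What to change.** Reword 8.5 and 9.2.5 to say that:

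- missing one or both calls does not exclude a patient;
- every patient with an immediate recall interview enters the immediate-recall analysis;
- each interview that was given is used in the planned mixed model;
- only the data of patients who withdraw consent are removed, as the consent terms require.

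Bring 11.4.1, 11.5 and the sample size text of the synopsis into line with this, and report follow-up completion by arm at days 7 and 30.

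The cost is a few sentences in an amendment. No additional data are collected, because the immediate interviews are already part of the schedule.

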## Trial specific preventive measures

NA. This is a study on communication.

## Concomitant Interventions (treatments)

No treatments.

## Study Drug / Medical Device Accountability

NA

## Return or Destruction of Study Drug / Medical Device

NA

# STUDY ASSESSMENTS

## Study flow chart(s) / table of study procedures and assessments

Eligible participants (see section on Participants above) will be asked to give written consent to participate in the study and complete a pre-discharge assessment. The pre-discharge assessment will take about 15 minutes and aims to collect basic demographic measures concerning each patient as well as a number of other measures that will serve as covariates in the analysis, such as patients’ health status, memory ability, state anxiety, state depression, and medical knowledge.

Immediately after the discharge communication event, patients will be interviewed for up to five minutes to assess recall of information provided during the discharge consultation and to assess patients’ satisfaction with the encounter.

Finally, two brief interviews of 5–10 minutes will be conducted over the phone seven days after discharge and 30 days after discharge to retest recall of discharge information, thus assessing the reliability of the main outcome measure and the time component of recall.

For more information see also section “study schedule”.

## Assessments of outcomes

The pre-discharge assessment will take about 15 minutes and aims to collect basic demographic measures concerning each patient as well as a number of other measures that will serve as covariates in the analysis, such as patients’ health status, memory ability, state anxiety, state depression, and medical knowledge. The rationale for including these measures is that they are potential moderators of participants’ recall of discharge information and thus should be included in the statistical analysis.

Immediately after the discharge communication event, patients will be interviewed for up to five minutes to assess recall of information provided during the discharge consultation and to assess patients’ satisfaction with the encounter.

Finally, two brief interviews of 5–10 minutes will be conducted over the phone seven days after discharge and 30 days after discharge to retest recall of discharge information, thus assessing the reliability of the main outcome measure and the time component of recall. In addition, patients will be asked about self-reported adherence to discharge recommendations, and overall assessment of the discharge consultation. Table 5 provides a description of the measures collected in each phase. Patients will also be asked about information provided by their General Practitioners to control for possible confounds of receiving extra or additional information from a third-party.

Table 5. List of Measures Used in Patient Interviews and Respective Description

| Phase | Measure | Description |
| --- | --- | --- |
| Pre-discharge  Assessment | Demographics | Age, Sex, Education, Marital Status, Nationality |
|  | Health-related quality of life | German version of the SF-12,^29^ a generic, short-form health survey with 12 items developed to provide a valid and reliable method to monitor subjective aspects of health and quality of life. |
|  | Memory | CERAD Word List Memory test, a free recall memory  test that assesses learning ability for new verbal information.^30^ A ten-item word list is presented over three trials (at the rate of 1 every 2 seconds) with a different word order each trial. The participant is instructed to read each word aloud as it is presented and then asked to recall as many words as possible. |
|  | State anxiety and depression | German version of the Hospital Anxiety and Depression Scale (HADS-D),^31^ a brief instrument containing two scales of 7 items assessing state anxiety and depression. |
|  | Medical knowledge | Multiple-choice test consisting of 6 questions of increasing difficulty developed by our research team. |
| Interview | Immediate recall | Patients will be asked to freely recall all information provided immediately after the discharge event, “Can you tell me all the information your physician just provided?”, and repeated use of prompts, “Was there any other information you can recall?” until the patient cannot recall any more information. |
|  | Satisfaction | Once patients cannot recall any additional information, they will be asked to characterize their satisfaction with the discharge communication event and physician. Specifically, we will previously developed items (see Study 4) asking patients to rate on a scale from 1 to 10 the (1) physician’s comprehensibleness, (2) information structuring, and (3) willingness to recommend the physician to family and friends. |
| Telephone Interview | Delayed recall | Patients will be asked to freely recall all information mentioned in the discharge event, “Can you tell me all the information your physician provided when you left the emergency department?”, and repeated use of prompts, “Was there any other information you can recall?” until the patient cannot recall any more information. In addition, patients will be asked whether they have received additional information from their general practitioner since discharge. |
|  | Adherence to recommendations | Patients will be asked to list all the physician recommendations that they have actively pursed, “Can you tell me which of your physician’s recommendations you have pursued?”. |
|  | Overall assessment | German version of the Patient Reactions Assessment (PRA-D),^32^ composed of three 5-item scales designed to measure information, affective, and communication components of physician–patient communication. |

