| **Measurements and Procedures:** | Study Procedure  The study involves two components: (a) the intervention component, consisting of the two physician-training programs and (b) the evaluation component, consisting of an assessment of the interventions through patient testing and interviews.  Physician Training  Physicians will be recruited to participate in the study, which will serve as a complement to physicians’ regular emergency department training. The two programs will follow the same structure, with physicians receiving the same intensity of teaching. Both programs will consist of one four-hour session of training with an experienced communication expert ([name] [name]). Also, both training programs will consist of theory and practice components as well as a test session to assess the actual use of communication skills. The information-structuring program will include a review of scientific evidence on the superiority of structured over non-structured communication as well as hands-on practical exercises in dyads to train structured communication skills. Specifically, participants will be introduced to the ‘InFARcT-scheme’ (categorization scheme that could, in principle, help physicians to structure information; for more information see: past work by research team) and trained to use it to structure their communication. The emotion skills training program will follow a similar structure but will focus on the NURSE communication model.^28^ The NURSE model encourages caretakers to engage in naming, understanding, respecting, supporting, and exploring patients’ emotional reactions with the goal of reducing anxiety and increasing compliance. In addition, physicians in both conditions will receive a one-hour booster session two weeks after the initial training involving a discussion of patient examples to whom they had applied the newly acquired skills. The rationale for the use of a booster session is to ensure that communication goals are maintained as a high priority and that physicians have a chance to receive additional feedback early in their training.  Patient Interviews  All physicians participating in the study will be asked to contact a member of the study team about any pending discharge communication with a patient suffering from chest pain or a patient suffering from abdominal pain. Eligible participants (see section on Participants) will be asked to give written consent to participate in the study and complete a pre-discharge assessment. The pre-discharge assessment will take about 15 minutes and aims to collect basic demographic measures concerning each patient as well as a number of other measures that will serve as covariates in the analysis, such as patients’ health status, memory ability, state anxiety, state depression, and medical knowledge. The rationale for including these measures is that they are potential moderators of participants’ recall of discharge information and thus should be included in the statistical analysis.  Immediately after the discharge communication event, patients will be interviewed for up to five minutes to assess recall of information provided during the discharge consultation and to assess patients’ satisfaction with the encounter.  Finally, two brief interviews of 5–10 minutes will be conducted over the phone seven days after discharge and 30 days after discharge to retest recall of discharge information, thus assessing the reliability of the main outcome measure and the time component of recall. In addition, patients will be asked about self-reported adherence to discharge recommendations, and overall assessment of the discharge consultation. Table 4 provides a description of the measures collected in each phase. Patients will also be asked about information provided by their General Practitioners to control for possible confounds of receiving extra or additional information from a third-party.  The discharge communication encounter as well as all interviews will be recorded with audio recording devices. |

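### The adherence question in Table 5 is not tied to the emergency discharge, so advice from a general practitioner could enter this secondary outcome

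*Protocol*

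**What the plan says.** Section 9.2 (Assessments of outcomes) gives the target of the measure: at the telephone interviews "patients will be asked about self-reported adherence to discharge recommendations". Section 11.4 (Planned Analyses) compares it between arms: "Similar models will be used to estimate the effect of the training programs on patient satisfaction, and adherence to discharge recommendations". Section 11.1 includes higher adherence in the hypothesis, next to better recall.

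The instrument is in Table 5, in the telephone-interview rows:

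- Delayed recall: "Can you tell me all the information your physician provided when you left the emergency department". The same row ends with "In addition, patients will be asked whether they have received additional information from their general practitioner since discharge".
- Adherence: "Patients will be asked to list all the physician recommendations that they have actively pursed", with the question "Can you tell me which of your physician’s recommendations you have pursued".

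The text of Section 9.2 gives the purpose of the GP item: "Patients will also be asked about information provided by their General Practitioners to control for possible confounds". The Synopsis (Measurements and Procedures) adds that "The discharge communication encounter as well as all interviews will be recorded with audio recording devices".

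**The concern.** The two telephone questions use the same term, *your physician*. The recall question ties it to leaving the emergency department; the adherence question ties it to nothing. A week or a month after discharge, a patient may have been advised by two physicians and may report what was done on the advice of either.

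The item matters for more than one outcome. Section 9.2.2 refers to Table 5 for medication adherence and disease management as well. Among the telephone measures listed there (delayed recall, adherence, overall assessment), only this question asks what the patient actually did after discharge. If its answers mix sources, the adherence comparison partly reflects contact with other physicians. Once the calls have been made, the source of each listed item cannot be fully recovered.

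**Working it through.** No arithmetic applies: the point concerns the wording of one interview item, and the protocol states no figure that depends on it. The check sets the relevant places side by side.

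1. **Target against wording.** Sections 9.2 and 11.4 both name recommendations given at discharge as the target. Neither the adherence question nor its description in Table 5 contains the emergency department, the discharge or the visit. The wording is wider than the target.

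2. **The neighbouring question.** Delayed recall, in the same call, uses the same term and adds the anchor. The means of fixing the referent is already in the table, and the adherence line lacks it.

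3. **Is GP contact foreseen?** Yes. The protocol asks about it as a possible confounder. Table 1 has two follow-up items that direct the patient to the family physician, chosen by 79% and 68% of the physicians in Study 1. These percentages are choices for one case vignette, not referral rates. Table 2 shows follow-up suggestions in 100% of the 20 talks of Study 3, but that covers the whole category, in which only two of nine items concern the family physician. GP contact before the calls is plausible; its frequency is unknown.

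4. **Does the GP item separate the sources?** As worded in Table 5 it asks whether information was received. A yes or no does not show which of several listed recommendations came from the GP. Adjusting for it in the model would not clearly help either, because GP contact happens after the physician's training has taken effect and may result from the discharge talk.

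5. **Does the recording separate them?** It could, if each listed item were checked against the recorded talk. The protocol states no such rule for adherence. Matching would remove advice that came only from the GP. It would not show which physician the patient was answering about when both gave the same advice, so it supplements the anchor and does not replace it.

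6. **Could the arms differ?** One arm is trained on a scheme that includes follow-up advice, so GP contact might differ by arm. Nothing in the protocol shows that it does. With equal contact, and equal misreading, the result would be added noise without bias between arms.

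**The case against.** Context does much to fix the referent. In the same call the recall question uses the same term for the emergency physician, explicitly anchored, and the GP is given a different name. Patients must be able to communicate in German, so the English line is presumably not what is spoken. The GP item exists precisely to control for third-party information, and the text of Section 9.2 describes it more broadly than Table 5 does, so it may capture content. All of this stands and lowers the likelihood of misreading. It does not remove it, because the only wording the protocol fixes is still unanchored.

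Two stronger readings are tempting, and neither is supported.

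- A reader might infer that GP advice *is* counted as adherence. The protocol gives no scoring rule, one may stand in an analysis plan or coding manual not shown, and the recordings would allow items to be checked. Only *could be* is supported.
- A reader might infer from the row order of Table 5 that the adherence question follows directly on the GP question. Table 5 is a list of measures, not an interview script. The Synopsis and the text of Section 9.2 mention the GP item after adherence and overall assessment, and Section 9.3.3 lists recall, adherence and overall assessment with no GP item between them. The order of asking is not fixed and may already be the preferable one.

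It is also fair to object to any false-positive rate attached to this point. The difference in GP contact, the items added per contact and the standard deviation would all have to be assumed, and the clustering by physician would have to be allowed for.

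**Conclusion.** The point holds in a limited form. The adherence question as fixed in Table 5 does not secure the construct that Sections 9.2 and 11.4 say it measures, and the GP item as worded there would not separate the sources afterwards. Advice from a GP may therefore contaminate a secondary outcome that is part of the stated hypothesis.

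No size can be given: the documents contain no GP-contact rate, no adherence standard deviation and no scoring rule, and the direction of any difference between arms is equally open. The conclusion assumes that some patients see a GP before the calls, which the protocol itself anticipates, and that the spoken German question is no more specific than the line in Table 5. The primary outcome does not depend on this question. This is an inexpensive improvement to a secondary measure, not a threat to the main result.

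**What to change.** Three changes to Section 9.2 and Table 5:

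1. Anchor the adherence question as the recall question is anchored, for example: *Which of the recommendations that the emergency physician gave you at your discharge from the emergency department have you followed?* Carry the anchor into the German wording.
2. State that this question is asked before the GP question.
3. State that only recommendations found in the audio-recorded discharge talk are counted.

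The first two cost one reworded line and one sentence on order. The third uses recordings that are already planned and adds some coding time to check listed items against them. No extra patients, visits or call time are needed. The first two must be in place before the calls they are meant to improve.
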